**2. Study Aims and Objectives**

The overall aim of this project is to evaluate the adherence club model compared to the clinic model of care. The two arms of the study will be early referral to the adherence club service (referral by study at 4 months post-initiation) and delayed referral to clubs (after 12 months post-initiation, referral to be done as per usual procedures).

- Primary objective

To compare adult HIV viral suppression up to 12 months post ART-initiation, among adults on ART with a suppressed viral load at 4 months, in those referred to the adherence club at 4 months, compared to those referred to the club after 12 months post-initiation.

- Secondary objectives

To compare the timing of entry into ART clubs, looking at outcomes such as:

- Retention in care ie missed visits and loss to follow-up
- Physical and mental health
- Acceptability of the ART service

This trial is a sub-study of the UCT PACART trial currently underway and as such the setting, population, study design, data management, ethical considerations and internal monitoring systems are designed to be in line with the PACART protocol as much as possible.

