**6. The standard ART Services at Gugulethu CHC – the clinic and the clubs**

The local standard of care is clinic-based from ART-initiation, with potential club referral from 6 months post-initiation for those patients who are virally suppressed and have no co-morbidities that require additional health care. Club referral is at the clinician’s discretion. The two models of care are described below:

Clinic care

The standard ART clinic service includes 2-6 monthly clinician reviews and medication refills (according to clinician discretion). Over the December/January holidays, patients receive 3 months of medication from the pharmacy (from mid-October to mid-November). Patients may send someone to collect their medication (“a buddy”) on their behalf. Patients with particular clinical or psychosocial concerns may be reviewed more regularly, or referred to higher levels of care. Patients in the clinic receive a waiting room health promotion and adherence talk (held daily). Standard clinic care includes blood tests at month 12 post-initiation (viral load and ART safety bloods as needed). There is no immediate follow-up for clinic defaulters, although every 4 months a list of those lost to follow-up is generated via the eKapa computer system, and those on the list will be visited at home depending on resources.

Club care

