There are currently 127 Adherence clubs operating at Gugulethu CHC. They meet in the nearby off-site community hall iKhwezi. Each club meets 2 monthly with the exception of the December/January holidays whereby the appointment interval is 4 months. The clubs are run by club counsellors who give a health promotion and adherence talk, promote condom use, weigh and check symptoms for each club member and dispense 2 months of pre-packed ART (4 months over the December/January holiday period). Each club receives an annual blood test visit at which point a nurse practitioner performs routine phlebotomy. The following visit is a clinical visit, at which the nurse practitioner checks the blood results and performs a clinical assessment. Patients in clubs may send someone (”a buddy”) to collect their ARTs for them, but only every alternate visit and never on a blood or clinical visit. If a participant misses a club visit, there is a grace period of 5 working days after the scheduled session for them to collect their medication. Those who have not collected their medication within this period are identified as defaulters. These defaulters are followed up by the counsellors via phone calls and home visits, depending on resources, and are removed from club. Patients are also removed from club if they have a high viral load (>400 copies/ml), are pregnant, or have any symptoms meriting further clinical assessment.

A comparison of clinic and club care is tabulated below:

| **AREAS OF CARE** | **MODEL OF CARE** (August 2016) |  |
| --- | --- | --- |
|  | **CLINIC** | **CLUB** |
| **Summary of model** | Seen in the Gugulethu ART clinic | Seen in an offsite hall, iKhwezi, as part of a club |
| **Usual eligibility criteria** | None – all patients on ARTs may attend | >6 months on ART, viral load<400, no other co-morbidities |
| **First appointment date** | Patients with a referral letter can present on any day. Date does not have to be booked with clinic | Patients referred to club must present to the club office, which is located at the clinic, with their clinic folder and referral letter. A counsellor then provides a date for the first visit, slotting the patient into a club with space available. |
| **Attending staff** | Clinician - CNP or doctor | Counsellor. CNP twice a year (blood visit and clinical visit) |
| **Prescription frequency** | 1-6 monthly, depending on clinician discretion | 2 monthly |

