| **Christmas holiday arrangments** | Pharmacy dispenses 3 months of ART from mid-October | Pharmacy dispenses 4 months of ART from the beginning of October. |
| **Buddy collections** | Buddies are unmonitored and are able to collect medication on behalf of the patient except when a clinician specifically requests to see the patient. | Buddies are able to collect medication on behalf of the patient on alternate visits, but blood and clinical visits must be attended by the patient. |
| **Counselling (lifestyle and adherence)** | Daily waiting room counsellor talk. Selected (high risk for non-adherence) patients receive pill checks and further counselling | Every club visit |
| **Blood tests** | CD4 annually only if CD4<200 | CD4 annually only if CD4<200 |
|  | Viral load (VL) at month 4, 12 and annually if on first-line regimen.  VL at month 6, 12 and annually if on second-line regimen.  If on tenofovir, creatinine is checked at month 1, 4, 12 and then annually.  If on zidovudine, Hb and differential white cell count is taken at month 1, 2, 3 and 6.  If on aluvia, cholesterol and triglyceride checked at month 3 and yearly if indicated. | VL annually, timing depends on when club blood visit scheduled.  If on tenofovir, creatinine is checked annually.  If on aluvia, cholesterol and triglyceride checked annually if indicated. |
| **Time spent at the location** | Varies from around 2 hours to the whole day. | 1-2 hours. Max around 3 hours for a clinical visit. |
| **Non-attenders follow-up** | Every 4 months, those patients who have not had an ART refill are visited at home by CCWs | Those who don't collect their medication within the 5 day grace period are called and visited (if resources allow) |
| **Procedure for VL 400-1000** | Repeat VL after 6 months | Referred back to clinic, then usual clinic protocols followed |
| **Procedure for VL >1000** | Refer to ROTF service | Referred back to clinic, then usual clinic protocols followed |

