For the **primary objective**, we hypothesize that adults randomized to early club referral will be more likely to maintain viral suppression (defined as <400 copies/ml, with secondary analyses at other thresholds) up to 12 months post-ART initiation, compared to adults randomized to delayed club referral.

Comparisons of study arms at enrolment will examine demographic, clinical and relevant behavioural variables. Primary analyses will be by intention-to-treat in participants with a VL <400 copies/mL. Secondary ‘per protocol’ analyses will be based on actual attendance at least one visit at the intended service. Additive binomial regression models will be used to assess the effect of trial arm on the primary outcome, with results presented as absolute risk differences with 95% confidence intervals. Models will be adjusted for clinical and demographic characteristics thought to predict the outcome while not mediating the intervention effect. Intervention effects will be examined across *a priori* subgroups including age, gender, previous antiretroviral exposure and nadir CD4 cell count.

For the **secondary objectives**, we hypothesize that adults randomized to early club referral will be more likely to be retained in care (defined as attending ART clinical appointments as scheduled), compared to adults randomised to delayed club referral. Analyses of other secondary outcomes (including measures of health status and health service utilization, as well as quantitative acceptability measures) will be based on pure-count methods, beginning with a description of variables overall and by arm using proportions with exact 95% confidence intervals, or median with interquartile ranges. Comparisons of distributions by trial arm will employ exact tests or rank-sum tests, as appropriate. Throughout statistical tests will be 2-sided at α=0.05, with the exception of primary outcome analyses that will be adjusted for interim looks (see below). Generalized linear models will be used to examine multivariable prediction of outcomes of interest. Models with repeated outcomes per subject over time will account for within-subject correlation through subject-specific random effects. Model fit will be compared using AIC and LR statistics; all modelling will employ standard diagnostic procedures.

Interim analyses

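### Retention is scored against each service's own appointment schedule, so the arms can differ in either direction when behaviour is identical

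*Combined protocol and SAP*

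**What the plan says.** Section 2 lists, as the first secondary outcome, "Retention in care ie missed visits and loss to follow-up"; neither component is defined there. Section 9 (Data analysis) states the hypothesis that early-referral adults will be "more likely to be retained in care (defined as attending ART clinical appointments as scheduled"). It gives no lateness window, no threshold, and no unit (per visit or per participant).

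Section 6 describes two services with different appointment rules:

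- **Clinic interval.** The text says "The standard ART clinic service includes 2-6 monthly clinician reviews and medication refills", at the clinician's discretion. The comparison table says "1-6 monthly, depending on clinician discretion".
- **Club interval.** "Each club meets 2 monthly with the exception of the December/January holidays whereby the appointment interval is 4 months".
- **Lateness.** For a missed club session, "there is a grace period of 5 working days after the scheduled session for them to collect their medication". No clinic equivalent is stated.
- **Buddies.** In the clinic, "Buddies are unmonitored and are able to collect medication on behalf of the patient" unless the clinician asks to see the patient. In clubs a buddy may collect only at alternate visits, and not at blood or clinical visits.
- **Detecting default.** Clubs identify it when the grace period ends and remove the member. The clinic relies on a list produced every 4 months.

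Section 5 gives everyone a clinic date one month after the month-4 visit. Section 7 cancels it for the early arm and states no cancellation for the delayed arm. Section 7 also keeps the delayed arm out of clubs until 12 months post-initiation, so these differences last for the whole 8 months of follow-up.

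**The concern.** An outcome defined by compliance with a schedule compares the arms fairly only if the schedule and the attendance rule are common to both. Here both come with the allocation. More scheduled visits mean more chances to miss one. A grace period in one arm turns some late collections into attendances. A buddy collection may or may not count, and buddies are available on different terms. Randomisation does not remove these differences, because they are part of what is randomised. Separating measurement staff from service staff does not help either, because the problem lies in the definition.

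Retention is the first secondary outcome listed and the only one with a directional hypothesis, and the Background gives it as a main reason for studying clubs. A reported benefit or harm on retention would be read as evidence about clubs when it might reflect only appointment rules.

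**Working it through.** **Plan's own figure.** No calculation is given for retention. The stated total of 214 is reproduced by a continuity-corrected comparison of 65% with 85% at 90% power and two-sided alpha 0.05: 107 per arm, and 2 x 107 = 214. I use 107 per arm below.

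**Visits in 8 months.**

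- Club: 8/2 = 4, or about 3 if the 4-month holiday interval falls inside follow-up.
- Clinic: about 2 (the 1-month date, then a 6-monthly review at about month 7), 4 if 2-monthly, 8 if monthly. Routine month-12 bloods could make the lowest count 3.

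**Null model (assumptions, not document figures).** On-date attendance per visit is q in both arms, visits are independent, and retained means every scheduled visit attended. With k visits, P(retained) = q^k. If a share g of late club attenders collect within the grace period, the club's q becomes q + (1-q)g.

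**Rejection probability.** Two-sided pooled z-test at 5%, n = 107 per arm. For club 4 v clinic 2 with q = 0.95 and g = 0:

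- 0.95^4 = 0.8145 and 0.95^2 = 0.9025, a difference of -0.088.
- Pooled proportion 0.8585; null SE = sqrt(0.8585 x 0.1415 x 2/107) = 0.0477; critical difference 1.96 x 0.0477 = 0.0934.
- Alternative SE = sqrt((0.8145 x 0.1855 + 0.9025 x 0.0975)/107) = 0.0473.
- P(reject) = Phi((0.0880 - 0.0934)/0.0473) = Phi(-0.11), about 45%. The other tail is negligible.

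**Results at q = 0.95, no true effect.**

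| Club visits | Clinic visits | Grace g | Club retained | Clinic retained | Club minus clinic (points) | P(reject) |
|---|---|---|---|---|---|---|
| 4 | 2 | 0 | 81.5% | 90.3% | -8.8 | 45% |
| 3 | 2 | 0 | 85.7% | 90.3% | -4.5 | 17% |
| 4 | 3 | 0 | 81.5% | 85.7% | -4.3 | 13.5% |
| 3 | 3 | 0 | 85.7% | 85.7% | 0 | 5% |
| 4 | 4 | 0 | 81.5% | 81.5% | 0 | 5% |
| 4 | 8 | 0 | 81.5% | 66.3% | +15.1 | 71% |
| 4 | 2 | 0.5 | 90.4% | 90.3% | +0.1 | 5% |
| 4 | 4 | 0.5 | 90.4% | 81.5% | +8.9 | 47% |
| 4 | 8 | 0.5 | 90.4% | 66.3% | +24.0 | 99% |

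**Sensitivity to q (g = 0).** For club 4 v clinic 2: -15.4 points (72%) at q = 0.90 and -3.8 points (22%) at q = 0.98. For club 4 v clinic 8: +22.6 points (92%) and +7.2 points (38%).

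**Scoring by share of visits attended.** The expected share is q whatever k is, so visit frequency no longer biases the mean. The grace rule still does: with q = 0.95 and g = 0.5 the club share is 0.95 + 0.05 x 0.5 = 0.975, a false +2.5 points. The buddy rules cannot be sized from the documents.

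**The case against.** The best defence is that Section 9 calls itself a brief outline and leaves a full analysis plan to the trial statistician, so the unit and window may still be settled. It also foresees random-effects models for repeated outcomes, so per-visit scoring is open, and that would remove the visit-frequency bias in the mean. Section 2 adds loss to follow-up, which need not depend on the schedule. All of this is fair, and it means that the all-visits model illustrates one possible scoring rule rather than the planned one. It does not clear the definition. Section 9 already ties retention to the schedule, per-visit scoring leaves the grace and buddy differences in place, and loss to follow-up is undefined.

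Three stronger readings are tempting, and the documents do not support them.

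- A reader might infer that the comparison must show a false deficit for clubs. The sign depends on the clinic interval, the holiday interval and use of the grace period. It is zero with equal visit counts and no grace effect, and close to zero where the biases offset, as in the row with 2 clinic visits and g = 0.5.
- A reader might take a 6-monthly clinic schedule to mean one visit in 8 months, which makes the gap larger. The 1-month clinic date, cancelled only for the early arm, already implies about two.
- A reader might call retention the main secondary outcome. The plan does not rank its secondary outcomes.

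**Conclusion.** The concern holds as a possibility of bias in either direction. As worded, the retention definition depends on a schedule and on attendance rules that differ by arm, and nothing in the plan harmonises them. With identical behaviour, all-visits scoring and 95% on-date attendance, the false difference runs from -8.8 to +15.1 points without a grace effect, over the visit counts shown. It reaches +24.0 points if half of late club attenders use the grace period and the clinic schedules monthly. The rejection rate runs from the nominal 5% to nearly certain. These figures rest on assumed attendance, independence, grace use and scoring; the documents supply only the intervals, the rules and the sample size. The actual size and direction cannot be known before the clinic intervals are seen. The primary outcome is an objective viral load, and neither it nor the 214 is touched. The definition should be changed, because the change is cheap and the outcome carries a stated hypothesis.

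**What to change.** Before the arm code is broken, replace the definition with one measure that uses the same event, window, buddy handling and data source in both arms. For example: in care at 8 months post-enrolment (12 months post-initiation) means ART supply in hand at that date, or a collection at any facility, by patient or buddy, within a fixed number of days after the last supply ended. The team should set the number of days in advance.

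- **Follow the records past visit 3.** Section 7 (Data abstraction) provides for consent to record review for up to 3 years after enrolment. A supply-gap rule cut off at visit 3 would bring the bias back. With a 90-day gap, for instance, a clinic patient given 6 months' supply at month 1 is covered to month 7 and could not fail before month 10. A club patient whose last 2-month supply was collected at month 2 runs out at month 4 and fails at month 7.
- **Long supplies that span the 8-month date.** Supply in hand is easier to satisfy with a long supply. As a sensitivity analysis, also report whether the next collection after that supply ended came within the window.
- **Removal from a club.** Count patients who continue at the clinic as in care.
- **Missed visits.** Report these descriptively within each arm, without a between-arm test.
- **Reconcile Section 6.** The clinic interval differs between the text and the comparison table, and the two must be made to agree.

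The cost is analysis-plan wording, dispensing dates and quantities added to the abstraction form (Section 7 lists attended-visit dates but not quantities), and a short extension of record review.

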The participant’s folder will be labelled with a sticker, signifying no referral to the club service to be done by the clinic staff. Those allocated to the delayed referral arm will also have their names entered onto a list to be held by the senior club counsellor and kept in the club office. This list will be checked when participants are referred to the club office and any participants on this list will not be given a club date and will be referred back to the attending clinician

Study visits

Including enrolment (study visit 1), there will be 3 study visits. These will be at enrolment and then at4 months and 8 months post-enrolment.

Measurements will be carried out by a study measurement team comprised of a research nurse and interviewers who operate separately from the routine ART services (adherence clubs and clinic). Visits will take place in a dedicated research space. The separation of routine services from study services will facilitate masking of trial assessments and retention activities.

At each study visit (estimated to last 1-2 hours), a standardized questionnaire will be used by the study interviewers to collect information and phlebotomy will be performed.

**At the enrolment visit and all subsequent study visits**, information will be collected on: demographics, past medical history and health care use, HIV disclosure, current ART use, relationship with health providers, mental health, alcohol and substance use, and social impact.

**Phlebotomy** will involve drawing 5ml of venous blood for storage and batched viral load testing. This same blood will be used (via pipetting from the PPT blood tube) for Dried Blood Spots (DBS). This pipetting method will be used to avoid a further procedure and its incumbent risks.

Laboratory measures

Participant venous blood (approximately 5ml at up to 3 study visits, totalling a maximum of 15ml over 8 months) will be drawn (using an PPT tube) at every study measurement visit. As previously described, some of this blood will be stored as a Dried Blood Spot, for use as an objective marker of adherence. The PPT tube specimen will be transported to the National Health Laboratory Service (NHLS) for testing.

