**9. Analytic considerations**

Sample size considerations

The projected sample size for the trial is 214 participants

This estimate is based on the following assumptions:

- A superiority comparison of the immediate and delayed club referrals.
- 90% power and a two-sided alpha of 0.05 using a log-rank test of survival proportions
- 1:1 randomization
- An expected proportion of virally suppressed adults in the delayed referral group of 65% (our best estimate of this is 68% from data collected at Gugulethu) and an expected proportion of adults in the early referral group of 85%. Thus the expected minimum difference in the primary outcome at 12 months post-initiation between the early and delayed arms is 20%.
- Furthermore, the proposed sample size will also provide >80% power to detect appreciable differences for most secondary outcomes of interest.

Data management

Data management will be as for the PACART study based at UCT and Gugulethu. Data collected on paper forms will be entered into a custom designed Microsoft Access database, maintained in a firewall-protected UCT server with nightly backups. The study database will be password-protected following standard password safety procedures. The database will be designed and maintained by a senior data manager who will develop the data dictionary, direct queries, and data quality assurance / quality control activities, and will supervise the data entry clerk. Data quality assurance will be in the form of robust database structure and platform, “front-end” data checks, including real-time database queries. Quality control will be through data checking scripts to identify out-of-range values, logic violations, and missing observations. Data editing will be based on reference to the form and/or source document in question; all data queries and responses will be logged, and edits will be implemented through separate program files. All study records will contain anonymous participant identification numbers, and no participant names or identifiers will be recorded.

Data analysis

Data will be exported to Stata Version 13.0 (Stata Corporation, College Station, Texas) or R (Gnu Project) for analysis. The full statistical analysis plan will be developed by the trial statistician as per the PACART trial. Here we provide a brief outline of planned analyses.

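### For the other secondary outcomes, the only stated comparison by arm is an exact or rank-sum test; the plan does not say that an enrolment-adjusted model will estimate the arm effect.

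*Combined protocol and SAP*

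**What the plan says.** Section 9 (Analytic considerations), under Data analysis, treats retention first and then the remaining secondary outcomes: health status, use of services, and acceptability ratings. These are to be summarised overall and by arm, as proportions with exact intervals or medians with interquartile ranges. Then: "Comparisons of distributions by trial arm will employ exact tests or rank-sum tests, as appropriate".

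Two modelling statements follow. One reads "Generalized linear models will be used to examine multivariable prediction of outcomes of interest". The other says that models with repeated outcomes will carry subject-specific random effects. Neither mentions trial arm or the enrolment value. In the primary-objective paragraph, by contrast, regression is tied to the effect of arm, with risk differences, 95% intervals and covariate adjustment.

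Section 7 (Research Procedures, Study visits) has the questionnaire given at enrolment and at both later visits, 4 and 8 months after enrolment. Its domains include health care use and "relationship with health providers, mental health, alcohol and substance use, and social impact". The schema in Section 3 puts the enrolment questionnaire ahead of randomisation, and Section 7 says that randomisation follows completed enrolment.

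Section 9 also describes its own text as an outline, with a full statistical analysis plan to follow.

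**The concern.** A person's enrolment score is usually among the best predictors of the same score later. Here it is collected before allocation, so adjusting for it cannot remove any of the intervention's effect. The one comparison by arm that the plan names cannot use it.

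Two things are at stake. The first is precision: physical and mental health are a named secondary objective in Section 2, and Section 9 claims more than 80% power for most secondary outcomes. The second is interpretability: a test plus separate summaries for each arm does not give the size of the difference between arms with its uncertainty.

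**Working it through.** **The plan's own figure.** The inputs, all from Section 9, are 65% against 85% suppressed, 1:1 allocation, and "90% power and a two-sided alpha of 0.05 using a log-rank test of survival proportions".

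- Two proportions, pooled: n = [1.960·√(2·0.75·0.25) + 1.282·√(0.65·0.35 + 0.85·0.15)]² / 0.20² = 96.4, so 97 per arm or 194 in total.
- With continuity correction: (96.4/4)·[1 + √(1 + 4/(96.4·0.20))]² = 106.2, so 107 per arm or **214**, an exact match.
- Log-rank by Freedman's formula: HR = ln 0.85 / ln 0.65 = 0.377, giving 52 events. At a mean event probability of 0.25 that is 208, within 3% of 214.

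The 214 is therefore accepted, and 107 per arm is used below.

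**Detectable difference without adjustment** (two-sided 5%, 80% power, full follow-up, in SD units):

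- t-test: (1.960 + 0.842)·√(2/107) = 0.383
- rank-sum, normal data: 0.383 / √(3/π) = 0.392

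**With the enrolment score as covariate.** If ρ is the correlation between enrolment and follow-up scores, the residual SD is multiplied by √(1 − ρ²), and the equivalent unadjusted trial size is 214/(1 − ρ²). The documents give no ρ, so 0.3 to 0.7 is an assumed range.

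| ρ (assumed) | √(1 − ρ²) | Detectable difference (SD) | Equivalent unadjusted total | Power at 0.30 SD |
|---|---|---|---|---|
| none (t-test) | 1 | 0.383 | 214 | 59% |
| 0.3 | 0.954 | 0.365 | 235 | 63% |
| 0.5 | 0.866 | 0.332 | 285 | 72% |
| 0.7 | 0.714 | 0.274 | 420 | 87% |

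Part of the step down from 0.392 (0.392 − 0.383 = 0.009 SD) comes from comparing means instead of ranks under normality, not from adjustment.

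**Simulation check** (4000 trials per setting, 107 per arm; normal case at a true difference of 0.383 SD). Entries are power at ρ = 0.3, 0.5 and 0.7.

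| Analysis | Normal scores | Log-normal scores |
|---|---|---|
| Rank-sum | 77–79% throughout | 78%, 78%, 77% |
| Linear ANCOVA, raw scale | 84%, 89%, 98% | 61%, 68%, 77% |
| Rank-based ANCOVA | 81%, 87%, 97% | 81%, 87%, 96% |

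Adjustment helps when the scale suits the data. Raw-scale linear ANCOVA on strongly skewed scores does worse than the planned test at 0.3 and 0.5.

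**Incomplete follow-up.** The plan gives no dropout rate. With an assumed loss of about 20% (86 per arm), the detectable difference is 0.437 SD by rank-sum, 0.427 SD by t-test, and 0.427 × 0.866 = 0.370 SD adjusted at ρ = 0.5.

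**The case against.** The strongest reply is that silence is not exclusion. Section 9 starts with description and tests and then moves to generalized linear and random-effects models. A repeated-measures model over three visits could use the enrolment score, as a covariate or as the first measurement. The section is also an outline that defers detail to a full analysis plan. This stands to the extent that a reader cannot conclude that the plan rejects enrolment adjustment. What remains is that the only analysis tied to a comparison by arm is a test without covariates, and that the models are tied to prediction or to within-subject correlation.

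Other parts of the reply also stand:

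- A reader might infer that the planned tests are biased by chance imbalance at enrolment. They are not: under randomisation their error rate already allows for it.
- A reader might infer that results would be bare p-values. Summaries by arm are planned; only an interval for the difference is missing.
- A reader might infer that the claim of more than 80% power is wrong. It cannot be tested, because no effect size is stated for any secondary outcome.
- A reader might extend the point to every questionnaire domain. Alcohol use is collected but not listed as an outcome, and no scored physical-health instrument is named among the domains. Acceptability and retention have no like-for-like enrolment value.
- The plan's use of medians suggests that skewed scores were expected. In that case a rank test is a reasonable default and raw-scale linear ANCOVA could be worse.

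**Conclusion.** This is a cheap improvement, not an error. The plan does not say which analysis gives the arm effect for these secondary outcomes, or how the enrolment value enters it. The stated default may therefore give up precision already available from the data. The point clearly covers mental health and health care use, and covers relationship with providers if that is analysed as an outcome.

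For roughly normal scores the detectable difference falls from about 0.39 SD to between 0.365 and 0.274 SD. The gain is minor at a correlation of 0.3 and substantial at 0.7. These figures rest on assumed correlations, 107 per arm and complete follow-up. With no correlation, adjustment gains nothing. The validity of the planned tests, the primary outcome and the 214 are not in question.

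**What to change.** In the full analysis plan, before arms are uncoded, list each secondary outcome score that is measured at enrolment. For each, state that the main comparison of arms is at 8 months, from a model of the follow-up score on arm with the enrolment score as covariate.

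Choose the scale in advance: proportional odds for ordinal scores, rank-based ANCOVA for skewed scores, a count GLM for counts, and linear ANCOVA only for roughly symmetric scores. Report the adjusted arm effect with a 95% CI where the model gives one, and keep the exact or rank-sum test as a sensitivity check. Leave retention and acceptability as planned. State whether the random-effects models are supportive or descriptive.

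The cost is a few sentences, slightly more modelling and some reliance on the chosen model form. No new data are needed.
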